### Participants, recruitment, inclusion criteria and randomisation

As this is a pilot study, the primary outcome is not the efficacy of the study intervention. Consequently, the sample size has not been calculated to ascertain efficacy. Instead, the method outlined by Viechtbauer *et al*
24 for calculating the sample size based on the probability of any issues that may arise has been used. A sample size of 40 using the above rationale is powerful enough to provide over 90% certainty of detecting any issues that occur with a probability of over 5%.

The study therefore aims to recruit 40 patients, all undergoing current treatment for opioid addiction and who smoke ten or more cigarettes a day. Participants will be recruited from the study site, an outpatient drug addiction treatment centre, either through self-referrals in response to advertisements shown in the treatment centre or referrals from treatment centre staff. Participants are eligible for inclusion if they want to quit smoking (complete abstinence), are aged between 18 and 65 years, undergoing pharmacological treatment for opioid addiction, smoke a minimum of 10 cigarettes per day and provide informed consent. Use of smoking cessation medication is not a criterion for exclusion. Participants will be ineligible for inclusion in the study if they exhibit insufficient English skills to understand study protocols, are currently undergoing treatment for other drugs of abuse or if taking part in other research. Pregnant women will not be excluded.

Participants will be randomised into either experimental (CM for abstinence) or control (CM for attendance) conditions when recruited into the trial. Randomisation will be performed by the principal investigator (PI), using the service provided by the company ‘sealed envelope’,^25^ and will be performed using random permuted blocks within strata. Randomisation will be stratified based on participants’ current smoking frequency (between 10 and 20 per day, and more than 20 per day^6^). All participants will be given at least 24 hours after being given an information sheet to decide whether to take part, and will provide written consent, collected by the PI ([name]).

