### Measures

#### Outcome measures

The primary outcome will be assessed by recording the number of participants completing the 5 weeks of the intervention in each condition. Success will be defined as 60% or more of participants completing treatment.

The secondary objectives of the study are to gather preliminary findings regarding the effects of the CM intervention on smoking in this group, and any possible effects the intervention may have on opioid addiction treatment outcomes. Smoking abstinence will be recorded as point prevalence and biochemically verified with abstinence defined as a breath CO reading of under 10 ppm^30^.Participants were informed that smoking cannabis would increase CO levels.

Participant medical records will be accessed after completion of the intervention to ascertain participants’ opioid addiction treatment, including treatment adherence, drug types (methadone, Subutex, so on), dosage and schedule (daily supervised pickup, weekly pickup, so on) as well as illicit drug use throughout the period of the trial.

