### Planned analysis

As the primary objective of the intervention does not entail any hypothesis testing, the only statistics reported for this will be descriptive, namely means and SD for the number of participants retained at the end of treatment in each condition. Baseline demographics will be compared between conditions using t-tests for continuous and χ^2^ test for categorical data to ensure that any differences in these are not driving any potential differences in retention.

For the secondary objectives, differences between the groups in smoking cessation will be investigated using χ^2^ test, differences between conditions on opioid use and opioid treatment during the intervention will be compared using t-tests and χ^2^ tests dependent on data and any questionnaire data will be reported using descriptive statistics. All statistics will be performed as two-tailed tests using an alpha value of 0.05.

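### The cessation test ignores the smoking stratum used in randomisation and the opioid comparisons use no baseline; the tests are valid, but they give up some precision, and significance testing suits a pilot's aim poorly

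*Protocol article*

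**What the plan says.** In the protocol article, the section on participants, recruitment, inclusion criteria and randomisation states: "Randomisation will be stratified based on participants’ current smoking frequency". The two levels are 10 to 20 and over 20 cigarettes daily, and allocation "will be performed using random permuted blocks within strata".

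The Planned analysis section does not mention this stratum. For smoking, "differences between the groups in smoking cessation will be investigated using" a chi-squared test. For opioid outcomes, "differences between conditions on opioid use and opioid treatment during the intervention will be compared using t-tests" or chi-squared tests, depending on the data. It adds: "All statistics will be performed as two-tailed tests using an alpha value of 0.05". Questionnaires are outside this point, because "any questionnaire data will be reported using descriptive statistics".

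The Outcome measures section says that opioid treatment data will be read from medical records after the intervention, including "drug types (methadone, Subutex, so on), dosage and schedule". Illicit drug use is read for the trial period. No value from before CM is named. The secondary objective is to gather preliminary findings on smoking and on opioid treatment outcomes, and the article says plainly that the sample of 40 was not sized for efficacy.

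**The concern.** There are three related weaknesses, all in methods that the article states.

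- **Stratum.** Permuted blocks within strata force the arms into balance on smoking level. If smoking level predicts quitting, an analysis that ignores it counts between-stratum variation as noise, and its standard error is too large.
- **Baseline.** Everyone is already on opioid pharmacotherapy at entry, prescriptions are reviewed every 6 months, and CM lasts 5 weeks. Dose and pickup schedule during CM will therefore plausibly resemble those just before it. A comparison of during-CM values alone would then carry a good deal of pre-existing difference between people.
- **Testing.** A pilot meant to inform a full trial needs an estimate and its uncertainty. A test at 0.05 with about 20 per arm will often be non-significant even when a useful effect exists.

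At stake is how much the planner of the full trial can learn from 40 people. The validity of the comparison is not in question.

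**Working it through.** **Inputs from the article.** N = 40; two arms; two strata; tests two-sided at 0.05. The article gives no figure for power, quit rates, SD or correlation in the secondary comparisons, so there is no plan figure to reproduce. Its sample-size statement concerns detection of problems and does not enter here.

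**Assumptions.** 1:1 allocation (20 per arm); equal strata (10 per arm in each); the quit rates and correlations shown below.

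**1. Variance of the risk difference.**
- Unstratified: [P(1−P) + Q(1−Q)]/20, where P and Q are the control and experimental quit rates averaged over strata.
- Stratified, equal strata: the sum of p(1−p) over the four arm-by-stratum cells, divided by 40.

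Worked example, scenario B (control 15%/5%, experimental 40%/20%, so P = 0.10 and Q = 0.30):
- Unstratified: (0.09 + 0.21)/20 = 0.015000
- Stratified: (0.1275 + 0.0475 + 0.24 + 0.16)/40 = 0.014375
- Reduction: 1 − 0.014375/0.015000 = 4.2%

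The power columns come from 100,000 simulated trials per scenario, without continuity correction. CMH is the Cochran-Mantel-Haenszel test.

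| Scenario | Control, by stratum | Experimental, by stratum | Variance, unstratified | Variance, stratified | Reduction | Power, chi-squared | Power, CMH |
|---|---|---|---|---|---|---|---|
| A | 20% / 10% | 40% / 30% | 0.01775 | 0.01750 | 1.4% | 31.2% | 30.8% |
| B | 15% / 5% | 40% / 20% | 0.01500 | 0.01438 | 4.2% | 35.2% | 35.9% |
| C | 20% / 5% | 50% / 20% | 0.01684 | 0.01544 | 8.3% | 38.9% | 40.8% |
| D (extreme) | 30% / 5% | 60% / 20% | 0.01922 | 0.01644 | 14.5% | 35.1% | 39.2% |

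**2. Type I error.** With no treatment effect and stratum quit rates of 15%/5% or 20%/5% in both arms, rejection rates were 3.6% and 4.0% for the chi-squared test, and 3.6% and 4.1% for CMH. Neither exceeds 5%.

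**3. Test against estimate.** For 10% versus 30% with 20 per arm, power is about 35%. The corresponding observed result, 2/20 versus 6/20, is a difference of 20 points. Its SE is √(0.09/20 + 0.21/20) = 0.1225, and 1.96 × 0.1225 = 0.240, so the 95% CI is about −4 to 44 points. With the stratified SE of scenario B, √0.014375 = 0.1199, the half-width is 0.235. Stratifying narrows the interval only from about ±24.0 to ±23.5 points.

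**4. Baseline adjustment of a continuous opioid outcome.** Adjustment multiplies the variance by 1 − ρ². The standardised difference detectable at 80% power is (1.960 + 0.842) × √(2/20) × √(1 − ρ²).

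| Assumed ρ | Variance reduction | Detectable difference (SD) | Equivalent N, 40/(1 − ρ²) |
|---|---|---|---|
| 0 | 0% | 0.89 | 40 |
| 0.3 | 9% | 0.85 | 44 |
| 0.5 | 25% | 0.77 | 53 |
| 0.7 | 49% | 0.63 | 78 |

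**The case against.** The strongest reply is that simple tests are a legitimate choice for a pilot. The outcomes are secondary, the sample was not sized for efficacy, and the article foresees no difference between arms at six months. Stratifying moves power by less than 2 points in the moderate scenarios, and in scenario A slightly downwards. Low power comes from N = 40, which no adjustment cures. Effect measures and intervals are commonly left to an analysis plan, and none is shown here. Logistic regression with several terms in 40 people would be fragile.

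Much of this stands. It limits the size of the point, rules out treating an unstated effect measure or interval as an omission, and argues against a multi-term logistic model. It does not remove the point, because the article names the tests, and an analysis plan that followed it would carry the same unadjusted tests forward. Sparse cells do not defeat a Mantel-Haenszel risk difference.

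A reader might also infer more than the documents support:
- *That the tests are biased or inflate type I error.* They do not; step 2 shows rejection below 5%.
- *That no usable effect estimate would result.* Arm counts and means still give an unadjusted difference and interval, and the article does not say that it will report P values alone.
- *That all secondary data are tested this way.* Questionnaire data are descriptive only.
- *That the stratifier was chosen because it predicts quitting.* The article gives no reason for it.
- *That methadone and buprenorphine doses will be pooled.* This is not stated; drug type is recorded alongside dose, and the choice of test depends on the data.
- *That pre-CM opioid values will be available.* This is plausible for people already in treatment, but it is not stated.

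**Conclusion.** The point holds as a modest loss of efficiency and a poor fit between method and aim, on secondary outcomes.

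- **Cessation.** The unadjusted analysis is valid. It gives up about 1–8% of the variance of the risk difference under moderate stratum effects and about 14% under an extreme one. This rests on equal strata, 1:1 allocation and assumed quit rates.
- **Opioid outcomes.** The possible gain is larger, 25–49% of variance, but it depends on an assumed correlation of 0.5–0.7 and on pre-CM values being in the records.
- **Testing at 0.05.** Power of about 35% for an assumed 10% versus 30% means that a non-significant result would say little. The estimate with its interval is what the next trial can use.

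**What to change.** In the Planned analysis section:

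1. Replace the chi-squared test for cessation with the Mantel-Haenszel risk difference stratified by the randomisation stratum, with a 95% CI, presented as an estimate and without a significance claim.
2. For continuous opioid outcomes, where the records hold a pre-CM value, report the mean difference between conditions adjusted for that value, with a 95% CI. Confirm first that the value can be obtained; if it cannot, report the unadjusted difference with its CI.
3. If dose is compared, compare it within drug type.

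The cessation change costs analysis wording only, since the stratum is known for everyone at randomisation. The opioid change needs one further value from each record that is already being opened. Neither makes the pilot precise: the cessation interval stays about ±24 points wide, and the report should say so.

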**Intervention:**

Escalating with reset CM as an adjunct to standard smoking cessation treatment. Financial incentives will be administered over a 5-week period for either biochemically verified abstinence from smoking or attendance at the clinic. Participants will be randomised to conditions stratified on current levels of smoking (high or low).

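### Smoking cessation is compared with a plain chi-squared test although randomisation is stratified by smoking level; the test is conservative, and can lose power, only if smoking level predicts quitting (minor)

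*Protocol article*

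**What the plan says.** The abstract, under Intervention, announces the stratification: "Participants will be randomised to conditions stratified on current levels of smoking (high or low"). The section on participants, recruitment, inclusion criteria and randomisation gives the cut: "Randomisation will be stratified based on participants’ current smoking frequency (between 10 and 20 per day, and more than 20 per day"). It also gives the method, which "will be performed using random permuted blocks within strata". The target size is stated there too: "The study therefore aims to recruit 40 patients".

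The Planned analysis section fixes the cessation comparison: "differences between the groups in smoking cessation will be investigated using" a chi-squared test. Opioid use and opioid treatment are to be compared by t-tests or chi-squared tests, depending on the data. All tests are two-tailed at 0.05. No test is said to use the smoking stratum.

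The same documents limit what these tests are for. On sample size: "Consequently, the sample size has not been calculated to ascertain efficacy". On the primary objective: "As the primary objective of the intervention does not entail any hypothesis testing, the only statistics reported for this will be descriptive". The Objectives section calls the smoking results preliminary, and Follow-up procedures says no difference between conditions is expected at 6 months.

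**The concern.** Blocking within strata keeps the arms close to balanced on smoking level. The difference between arms in quit rate therefore no longer contains chance imbalance on that factor. A pooled chi-squared test still calculates its error as though such imbalance could occur. If smoking level predicts quitting, the standard error is too large, the test rejects less often than 5% under the null hypothesis, and some of the precision bought by stratifying is lost.

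Smoking level is the only stratification factor, so the designers presumably thought it might matter to outcome. The Discussion presents the pilot as a step towards a full-scale trial. The cessation estimate and its uncertainty are therefore among the useful outputs, and it is worth having the analysis match the design.

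**Working it through.** **Figures in the plan.** The protocol states no quit rate, stratum effect, effect size or power for any comparison between arms, so there is no figure on this point to reproduce. The one probability attached to the 40 participants concerns detecting problems in a pilot. For a problem with probability 5% it is 1 − 0.95^40 = 87.1%, short of the stated 90%. That is a separate matter and does not affect what follows.

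**Inputs.** From the protocol: 40 participants, two strata, permuted blocks within strata, chi-squared test, two-sided 0.05. Assumed: 1:1 allocation (20 per arm), 10 per arm in each stratum unless stated, the control quit rates shown, and a common treatment odds ratio (OR).

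**Mechanism, under the null hypothesis with equal strata.** The pooled test uses variance p(1 − p), where p is the mean of the stratum rates p1 and p2. The actual variance of the arm difference depends on the within-stratum mean, [p1(1 − p1) + p2(1 − p2)]/2. Let r be the second divided by the first. The approximate true size is 2[1 − Φ(1.96/√r)].

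- 50%/10%: p = 0.30; r = 0.170/0.210 = 0.810; 1.96/0.900 = 2.18; size about 2.9%.
- 40%/10%: p = 0.25; r = 0.165/0.1875 = 0.880; 1.96/0.938 = 2.09; size about 3.7%.
- 20%/10%: p = 0.15; r = 0.125/0.1275 = 0.980; 1.96/0.990 = 1.98; size about 4.8%.

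**Check by exact enumeration and by simulation (200,000 trials per scenario).** The uncorrected Pearson chi-squared test is compared with the uncorrected Cochran-Mantel-Haenszel (CMH) test, both rejecting above 3.84. The two methods agree to about 0.2 of a point.

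| Control quit rates (lighter/heavier smokers) | Treatment OR | Size, plain v CMH | Power, plain v CMH | Gain from stratifying |
|---|---|---|---|---|
| 50%/10% | 6 | 3.2% v 4.9% | 52.9% v 66.0% | +13.1 |
| 40%/10% | 5 | 3.8% v 4.8% | 51.9% v 59.7% | +7.8 |
| 30%/10% | 5 | – | 58.0% v 60.7% | +2.7 |
| 25%/10% | 5 | 4.6% v 4.8% | 59.5% v 60.2% | +0.7 |
| 20%/10% | 5 | 4.7% v 4.8% | 59.0% v 58.5% | −0.5 |
| 15%/10% | 6 | – | 67.7% v 66.5% | −1.2 |
| 20%/20% | 4 | – | 53.1% v 50.7% | −2.4 |

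The odds ratio between strata is 9.0 in the first row (1.0/0.111), 6.0 in the second (0.667/0.111), 3.9 in the third (0.429/0.111) and 1 in the last.

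**Why stratifying can lose a little.** The CMH variance for a stratum with n per arm carries a factor 2n/(2n − 1) that the pooled test lacks. With n = 10 this is 20/19 = 1.053. If smoking level explains nothing, the stratified statistic is therefore about 5% smaller.

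**Unequal strata.** With 6 lighter and 14 heavier smokers per arm, rates 40%/10% and OR 5, power is 51.6% v 55.9%, a gain of 4.3 points. With 14 lighter and 6 heavier, rates 20%/10% and OR 5, it is 62.0% v 60.8%, a loss of 1.2 points.

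**The case against.** The strongest reply has four parts.

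- **The gain rests on assumed stratum effects.** The protocol gives no evidence that the two smoking bands differ in quit rate. With modest differences the gain vanishes or turns into a small loss, as the lower rows of the table show. This stands. A reader might infer that ignoring the stratum always costs power; the documents give no stratum effect on which to base that.
- **The plain test is valid.** This also stands. Its size is at or below about 5% throughout, so there is no added risk of a false positive. Nor does stratifying always restore the nominal level: at control rates of 10%/5% both tests have size about 2.5%, because the counts are small and discrete.
- **No decision depends on the test.** The primary outcome is completion of the 5 weeks, judged against 60% and reported descriptively, and the sample size was not set for efficacy. This stands and limits the severity.
- **A condensed article may leave stratum adjustment to a fuller plan.** This stands only in part. A fuller plan may name a stratified test, but the article names the test and the alpha, and read as written that is an unstratified comparison.

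A reader might also extend the point to every comparison between conditions. The baseline comparisons are not affected. For opioid outcomes nothing in the protocol links cigarettes per day to the result. With an assumed standardised difference of 0.8 and 20 per arm, power would rise from 71.6% to 73.7%, 76.0% or 80.7% if the stratum explained 5%, 10% or 20% of the variance, but the documents support none of those shares.

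**Conclusion.** The mismatch is real for smoking cessation: the trial randomises within smoking-level strata and the stated test ignores them. The consequence is conditional. With control quit rates of 40–50% against 10%, the plain test runs at about 3 to 4% instead of 5%. With 30–50% against 10%, it loses about 3 to 13 points of power. With a weak or absent stratum effect the tests are about equal, and stratifying costs up to about 2 points. These sizes rest on 20 per arm, the assumed quit rates and treatment odds ratios of 4 to 6.

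Severity is minor. The comparison is preliminary, secondary and unpowered, and the error runs only in the conservative direction. The change is still worth making, because its largest cost in the scenarios examined is 2.4 points and its largest gain is 13.1.

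**What to change.** In Planned analysis, replace the plain chi-squared test for smoking cessation with a Cochran-Mantel-Haenszel test, and report a Mantel-Haenszel risk difference with its 95% confidence interval, both stratified by the randomisation stratum (10 to 20, more than 20 a day). A stratum term for continuous opioid outcomes is optional. Leave the baseline comparisons as they are.

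The cost is one sentence of analysis wording. The stratum is recorded for every participant at randomisation, so nothing further need be collected. The price is the small loss of power noted above if smoking level turns out not to predict quitting.

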### Objectives

Primary objective: To investigate whether a CM intervention can be successfully added to standard stop smoking services treatment, in patients undergoing outpatient treatment for opioid addiction, in order to identify any elements that need changing before carrying out a full-scale randomised controlled trial (RCT).

Secondary objective: To gather preliminary findings regarding the effects of the CM intervention on smoking in this group, and any possible effects the intervention may have on opioid addiction treatment outcomes.

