### Follow-up procedures

Six months after their set quit date, participants will be contacted by the PI to ascertain their self-reported smoking status. The main purpose of this follow-up is to ascertain whether participants can be successfully followed-up for 6 months, and no group differences are expected to be found between the different conditions. To test the optimal follow-up method, participants will be pseudo-randomised by recruitment order to be contacted by text and phone call, or email and phone call. All participants will also be asked to return to the clinic in order to have their breath CO levels tested to verify abstinence. Once this is done, participants will have completed their participation in the study. Participants will receive a £10 voucher for completing the follow-up procedure.

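### Between-condition effects on smoking and opioid outcomes are planned only as tests at 0.05, although the objective is preliminary and the sample was not sized for efficacy (minor)

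*Protocol article*

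**What the plan says.** The secondary objective (Objectives) begins: "To gather preliminary findings regarding the effects of the CM intervention on smoking in this group". Its second part covers the outcomes of opioid treatment.

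The section on participants, recruitment and randomisation sets the target at 40 and states: "the sample size has not been calculated to ascertain efficacy". The number was chosen instead by the chance of meeting practical problems.

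The Planned analysis section treats the two objectives differently:
- Primary objective (retention): descriptive statistics only, because no hypothesis is tested.
- Secondary objectives: a chi-squared test for cessation, t-tests or chi-squared tests for opioid use and opioid treatment, and descriptive statistics for questionnaire data.

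It closes: "All statistics will be performed as two-tailed tests using an alpha value of 0.05". The article names no risk difference, mean difference or confidence interval for the smoking or opioid comparisons.

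**The concern.** A preliminary look at effects should give the size of the difference and its uncertainty, which is what the design of a full-scale trial needs. A test at 0.05 gives neither. In a sample not sized for efficacy, it often returns a non-significant result even when the true difference is worth pursuing. For opioid outcomes, a non-significant test leaves a sizeable worsening open, and the p-value alone does not show this.

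The unqualified chi-squared test also leaves the verdict partly undetermined. When quitters are few, the versions of the test can fall on opposite sides of 0.05.

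**Working it through.** **Inputs.** From the protocol: N = 40, two arms, two-sided alpha 0.05. Assumed, because the article gives neither: 1:1 allocation (20 per arm) and all quit rates.

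**The plan's own figure.** The sample-size paragraph claims more than 90% certainty of detecting problems with a probability above 5%. At exactly 5%, 1 − 0.95^40 = 0.871. Reaching 90% takes ln(0.10)/ln(0.95) = 44.9, so 45 participants, or a problem probability of about 5.6% at N = 40. That is a separate matter; what follows uses only N = 40.

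**Power of the chi-squared test.** With a and b quitters out of 20 and p̄ = (a + b)/40, z = [(a − b)/20] / √(p̄(1 − p̄) × 2/20). Power is the sum of Bin(a; 20, p1) × Bin(b; 20, p2) over all tables with z² ≥ 3.84 (uncorrected test).

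| Assumed quit rates | Difference | Power | Non-significant |
|---|---|---|---|
| 10% v 20% | 10 points | 14% | 86% |
| 20% v 30% | 10 points | 11% | 89% |
| 10% v 30% | 20 points | 36% | 64% |
| 20% v 40% | 20 points | 29% | 71% |
| 5% v 25% | 20 points | 44% | 56% |
| 20% v 50% | 30 points | 53% | 47% |
| 10% v 40% | 30 points | 62% | 38% |
| 5% v 35% | 30 points | 72% | 28% |

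The 64 to 86% range describes 10% v 20%, 10% v 30% and 20% v 40%. It is not a bound: 20% v 30% lies slightly above it and 5% v 25% below it. Fisher's test has less power: 7%, 24% and 19% for those same three pairs.

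**t-test.** With 20 per arm, 80% power needs a standardised difference of 0.91 (noncentral t, 38 degrees of freedom). The normal approximation gives (1.96 + 0.84) × √(2/20) = 0.89.

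**What an interval adds.**
- 6/20 v 2/20: p̄ = 0.20, z = 0.20/√(0.20 × 0.80 × 0.10) = 1.58, p = 0.11. The Wilson limits are 0.145 to 0.519 and 0.028 to 0.301. The Newcombe lower limit is 0.20 − √(0.155² + 0.201²) = −0.054, and the upper limit is 0.20 + √(0.219² + 0.072²) = 0.431. The result is +20 points, 95% interval −5 to +43.
- 4/20 v 4/20: p = 1.0, but the interval is −25 to +25 points.

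**Dependence on the version of the test (p-values, 20 per arm).**

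| Quitters | Uncorrected | Continuity-corrected | Fisher |
|---|---|---|---|
| 0 v 4 | 0.035 | 0.114 | 0.106 |
| 1 v 6 | 0.037 | 0.096 | 0.091 |
| 2 v 8 | 0.028 | 0.068 | 0.065 |

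Expected quitters per arm in these tables are 2, 3.5 and 5. Summing the binomial probabilities of all tables where the corrected and uncorrected verdicts differ gives 9% of trials at 10% v 20%, 14% at 10% v 30% and about 12% at 20% v 40%.

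**The case against.** The strongest reply is that naming a test does not exclude reporting estimates. When the authors mean exclusively, they say so, as they do for the primary objective; the sentence on secondary objectives carries no such restriction. The alpha sentence most naturally sets sidedness and level for whatever tests are run. It cannot mean that nothing but tests is reported, since questionnaire data in the same paragraph are descriptive. Effect measures, interval methods and test versions are often left to an analysis plan, and none is shown. If counts per arm are published, a reader can derive the interval.

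Much of this stands. A reader might infer that estimates will be withheld, that a non-significant result will be read as no effect, or that opioid outcomes will be declared unharmed. The article says none of these, and it makes no significance result a condition for going on to a full trial. A reader might also infer that the tests would usually be non-significant whatever the true effect; the 30-point rows show otherwise.

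Nor does the Follow-up procedures section help the case. Its remark that "no group differences are expected to be found between the different conditions" concerns the 6-month follow-up, whose main purpose is to see whether participants can be followed up. It does not contradict a comparison during or at the end of treatment.

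What survives is narrower. The plan does not leave the method open: it states tests and a threshold as the analysis of these effects, and a better-suited method is available at the same sample size.

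**Conclusion.** The point holds as a minor improvement. For the smoking and opioid effects, the only named between-condition analysis is a test at two-sided 0.05, which suits neither a preliminary objective nor a sample not sized for efficacy.

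With 20 per arm and quit rates of 10 to 20% in the lower arm, a true difference of 10 to 20 points would be missed about 64 to 86% of the time on the pairs 10% v 20%, 10% v 30% and 20% v 40%. At about 30 points power is 53 to 72% (the upper figure needs a 5% lower rate), so the claim stops there. The dependence on the test version is real but confined to tables near the threshold.

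All these figures rest on assumed rates and assumed equal allocation. The primary outcome and trial conduct are unaffected. Intervals as wide as −5 to +43 points will not settle efficacy; they show plainly how much remains open.

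**What to change.** In the Planned analysis section, for the secondary objectives:

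1. Make the between-condition difference with its 95% confidence interval the main result: a risk difference with a score or Newcombe interval for cessation and other binary outcomes, and a mean difference for continuous opioid outcomes.
2. State that no claim of effect, or of no effect, will rest on p-values.
3. If a p-value for cessation is still quoted, name one small-sample test in place of the unspecified chi-squared test.

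The cost is wording only, with no extra data or recruitment. The downside is that the pilot gives up a significant / not significant statement that it was not sized to make.
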